# **Research title**

**Effectiveness of a dietician-led dietary intervention in reducing Glycated Hemoglobin among type-2 diabetes patients: an open-label, randomized controlled trial**

# **Project summary (~250 words)**

Diabetes mellitus is one of the major intractable public health problems in developing countries including Nepal. The dietary approach is of paramount significance in the management of type 2 diabetes. There is still a lack of evidence on a dietitian-led dietary approach to the management of T2DM patients in the Nepalese context. The aims of this study is to examine the effectiveness of dietitian-led dietary approach to management of diabetes on reduction of HbA1c level, nutrition education score and macronutrient intake among T2DM patients in a tertiary care hospital in Kathmandu, Nepal.

The Dietary Approach to the Management of Diabetes (DIAM-D) trial is a hospital-based, open-label, two-armed, randomized control trial. A total of 156 participants with T2DM having HbA1c >6.5% will be enrolled in the study. Participants will be consecutively enrolled and assigned to receive nutrition education and counseling (NEC) and diet plan in the intervention group (n=78) and usual routine care in the control group (n=78) randomly. The NEC will be provided to participants on group session and the diet plan will be face-to-face individual basis at the time of enrollment and follow-ups will be done every month. Baseline data will be collected using a structured questionnaire for an interview and the biochemical tests will be measured. Baseline data will be collected at the time of enrollment, midline in three months and end-line data collection in 6 months. The primary outcome of the study will be a difference in mean change (from baseline, midline to 6 months) in the HbA1c level between the two study arms from baseline to end line. The secondary outcomes measure will be changed in biochemical and clinical parameters between the two arms at baseline midline to six months. Data will be entered using Epidata Software and transferred to the STATA/MP version 14.1 for further analysis. Data will be analyzed using an intention-to-treat basis. Independent sampele t-test will be used to estimates changes between the intervention and usual care arms.

**Key word:** Dietitian, Dietary approach, Management, Diabetes, Nepal

# **Introduction**

Diabetes mellitus (DM) refers to the metabolic syndrome characterized by high blood glucose levels considering major public health problems globally ^1^. The global prevalence of diabetes in adults has been increasing over the decades ^2^. According to the world health organization (WHO), diabetes is the seventh leading cause of death accounting for 1.59 million deaths in 2016 ^3^. According to the International Diabetes Federation (IDF) data, it was estimated that among 18-99 years, there are 451 million people with diabetes globally. The number projected to increase to 693 million by 2045 ^4^. The rapid change of diabetes prevalence in many countries specially developing countries have been influenced by rapid urbanization and drastically changes towards the sedentary lifestyle^2^. Similarly, an increase in the prevalence of diabetes is characterized by various modifiable and non-modifiable risk factors, modifiable risk factors include changes in dietary habits and sedentary lifestyle which contributed to overweight/ obesity and non-modifiable risk factors including genetic cause and age ^5^.

The prevalence of diabetes mellitus in the south Asian region was a rapid increase over the last two decades ^6^. According to the International Diabetes Federation (IDF) data for Nepal, the prevalence of T2DM in the 20-79 years age group was 4% in 2017 and the predicted number of undiagnosed cases was 532,100. IDF estimates the prevalence projected to increase by 6.1% and 1,264,200 undiagnosed cases in 2045 in Nepal^7^. Evidence from systematic review and meta-analysis done by Gyawali et al, (2014) also reported that the prevalence of diabetes is a major public health problem with a prevalence rate of 8.4% ^8^. Dhimal et al. conducted a nationwide cross-sectional population-based study carried out from 2016-1018 found that the prevalence of diabetes was 8.5%^9^. Diabetes is the third most common non-communicable disease in Nepal, which causes 12% of all hospitalizations^10^.

# **Rationale and Justification of study**

The prevalence of type 2 diabetes mellitus (T2DM) has drastically increased in recent years in Nepal^11^. T2DM is accompanied by complications such as dyslipidemia, hypertension, and obesity. Several studies have shown that these complications can be prevented if lowering the HbA1c level and which has to be maintained within normal limits^12^.

Dietary management is considered as the cornerstone of blood glucose level control in T2DM patients^13^. Nowadays, nutrition education and counseling are the widely accepted strategies for the management of diabetes^14^. Various studies have shown that T2DM patients are an association with nutrition education and improving dietary habits, nutritional knowledge and improving clinical outcomes such as lower blood glucose and HbA1c levels^13–15^. Once the diagnosis is confirmed to T2DM, patients are managed by mainly three approaches such as diet alone, diet and drugs or diet and insulin^16^. Indeed, dietary factors are crucial for the management and prevention of T2DM ^13^. Furthermore, individualized nutrition education and counseling are effective strategies in adherence to diet recommendations and in improving glycemic control^12^. Dietitian-led nutrition education and lifestyle intervention are effective in reducing body weight and glucose-related outcomes^1^. However, limited studies have been carried out to examine the effectiveness of a dietary approach to the management of diabetes consulted by a dietitian in developing countries ^17,18^. Therefore, there is still a lack of evidence on effective guidelines and protocols for a dietitian-led dietary approach to the prevention and management of T2DM patients.

# **Objectives**

## **General objectives:**

The main objective of this study is to evaluate the effectiveness of dietitian-led dietary approach to management of diabetes on reduction of HbA1c level, nutrition education score and macronutrient intake among T2DM patients in a tertiary care hospital in Kathmandu, Nepal.

## **Specific objectives:**

- To measure the change in HbA1c level among T2DM patients between the intervention and control/usual care arm.
- To evaluate the change in macronutrient intake level among T2DM patients in the intervention and usual care arm.
- To assess dietitian-led nutrition education and counseling on nutritional knowledge of diabetes among T2DM patients.
- To evaluate the change in biochemical parameters among T2DM patients in the intervention and usual care arm.
- To assess the nutritional status such as BMI and WHR among T2DM patients

# **Research questions/hypothesis**

Dietitian-led dietary approach to the management of diabetes will improve on HbA1c level, nutrition knowledge score and macronutrient intake level compared to usual care among type 2 diabetes mellitus patients in tertiary care hospital in Nepal.

# **Research design and Methodology**

This study will adhere to the Consolidated Standards of Reporting Trials (CONSORT) 2010 updated guidelines for reporting for RCTs ^19^.

## **7.1. Research method**

a. Quantitative

## **7.2. Types of study**

a. Experimental/Interventional: The proposed study is a randomized, controlled, open-label trial to evaluate the effectiveness of dietitian-led dietary approach to management of diabetes on reduction of HbA1c level and macronutrient intake among T2DM patients in tertiary care hospital in Kathmandu, Nepal (Figure 2). This study utilized two-arm RCT with equal allocation of participants between the intervention and control group/usual care arm. The intervention will include a dietitian-led nutrition education, counseling session and individual basis diet plan emphasis on glycemic control diet targeted to T2DM patients attending during the OPD visits in hospital.

## **7.3. Study population/Sampling frame**

The source of the population of the study in both intervention and control group will be known cases of T2DM and newly diagnosed cases of T2DM patients who are within 25-64 years of age group attending the OPD of the hospital.

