## **7.7. Inclusion and Exclusion criteria**

**Inclusion Criteria:**

- Diagnosis of type 2 diabetes
- HbA1c>48 mmol/mol (6.5%) at time of diagnosis ^21^
- male or female aged ≥24-64 years and visited in OPD of target hospital
- Those who give consent to participate in our intervention study

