**Independent variables**

- - **Socio-demographic information (from Baseline):** Age, Sex, Education level, Occupation, Religion, Marital status, Residence, Smoking habit, and Alcohol habit
  - **Clinical and biochemical parameters (baseline end line):** HbA1c, fasting blood glucose, Systolic diastolic blood pressure, Lipid profile, Quality of life, Body mass index (BMI), Waist hip ratio (WHR), Physical activity level, Current medication used
  - **Dietary intake (baseline end line):** Carbohydrate, Fat, Protein, Food groups, Nutritional knowledge score on diabetes.

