**Tools and procedure**

- Screening checklist: This checklist entails information regarding inclusion and exclusion criteria.
- Baseline questionnaire: The study participants’ information on Socio-demographic, such as age, sex, occupation, educational level, residence, religion, ethnicity, etc. will be taken by using a face-to-face structured questionnaire interview. The questionnaire will be adopted from NDHS 2017 and STEP Survey 2019^22,23^.
- Dietary intake: Dietary intake assessment will be assessed before intervention (baseline) and after intervention (end line) using 24-hour qualitative dietary recall and food frequency questionnaire (FFQ) to compute the macronutrient intake level.
- Biochemical measurements: A fasting blood sample for HbA1c, fasting glucose, liver function test (bilirubin, ALT, AST ALP, and albumin) and lipid profile (total cholesterol, triglycerides, HDL, LDL) will be measured at baselines, three months and six months. All blood samples will be taken and handled, analyzed and disposed of according to local practice policy.
- Quality of life: The Problem Areas in Diabetes (PAID) score^24^, a 20 items questionnaire measuring the problems related to emotions, treatment, food and social support, will be measured at baselines and 12 months.
- Physical measurement: Height will be measured using a stadiometer to the nearest 1cm. Participants' weight will be measured to the nearest 0.1kg using the Seca weighing scale. BMI will be measured calculated using the widely used formula (BMI= weight (kg)/height (m)^2^), and waist Hip Circumference (WHR) will be measured using measuring tape. Systolic and diastolic blood pressure will be measured three times after 5 minute seated rest using a sphygmomanometer and stethoscope. The trained data enumerator will be taking physical measurements according to the study manual procedures.
- Nutritional knowledge score on diabetes: The diabetes knowledge test (DKT)^25^will be used to assess the nutritional knowledge score on diabetes.
- Physical activity: The physical activity will be measured using the Global Physical activity questionnaire recommended by WHO STEPwise surveillance tools^23^.
- Monitoring checklist: This will be used as every month follow up checklist. The information on lifestyle modification such as consumption of food, physical activities, adherence, and diabetic-related minor and major complication will be sought.

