## **7.12. In case of RCT, process of randomization and blinding, description of stopping rules for individuals for part of the study or entire study, the procedures and conditions for breaking the codes etc.**

The dietitians and enumerators will explain the purpose of the study to the participants and those participants who willing to give written informed consent and meet the inclusion criteria will be randomly assigned to either the intervention or the usual care arm. Once participants sign an informed written consent form, he or she will be enrolled in the study. Eventually, participants will be enrolled in either intervention or control groups randomly using computer generated random numbers.

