**Main Study Questionnaire in English - Baseline/End line**

| **Participants Information** | | | |
| --- | --- | --- | --- |
|  | Response | | Code |
| Study Group | Control 0  Intervention 1 | |  |
| Date |  | |  |
| Participants ID |  | | I1 |
| Participants full name |  | | I2 |
| Contact number |  | | I3 |
| Baseline interview date |  | | I4 |
| Follow-up date |  | | I5 |
| End line interview date |  | | I6 |
| Consent has been read and obtained | Yes  No | 1  2  If no, End | I7 |
| **Section 1: Socio-demographic information, Baseline** | | | |
| Sex ( record male/female as observed) | Male  Female | 1  2 | C1 |
| How old are you | …….years |  | C2 |
| What is your education level? | No formal education  Primary (1-5)  Secondary (6-10)  Higher secondary(11-12)  Bachelors and above  Refused | 1  2  3  4  5  88 | C3 |
| What is your ethnic background?  (Refer to caste classification: CC1 ) | Dalit  Disadvantaged Janajati  Relatively advantaged Janajati  Disadvantaged Non-dalit Terai caste group  Religious minorities  Upper caste group  Others  Refused | 1  2  3  4  5  6  7  88 | C4 |
| What is your religion? | Hindu  Buddhist  Muslim  Kirat  Christian  Others  Refused | 1  2  3  4  5  6  88 | C5 |
| What is your marital status? | Never married  Married  Separated/divorced  Widowed  Cohabiting  Refused | 1  2  3  4  5  88 | C6 |
| Which of the following best describes your main occupation? | Government employee  Non-government employee  Self-employed  Students  Homemaker  Retired  Unemployed  Others  Refused | 1  2  3  4  5  6  7  8  88 | C7 |
| Where do you live? | Urban  Rural | 1  2 | C8 |
| How much is your average monthly Income? | Rs | ……… | C9 |
| Family history of Diabetes Mellitus | Yes  No | 1  2 | C10 |
| **Section 2: Behavioral information Baseline/Endline** | | | |
| **Tobacco use** | | | |
| Do you currently smoke any tobacco products, such as cigarettes, bidis, cigars, pipes, hukahs, or tamakhus? | Yes  No | 1  2  If No, go to A1 | T1 |
| How frequently do you smoke tobacco products? | Daily  5-6 days a week  3-4 days a week  1-2 days a week  Occasionally | 1  2  3  4  5 | T2 |
| In the past, did you ever smoke any tobacco products? | Yes  No | 1  2  If No, go to A1 | T3 |
| In the past, how frequently did you smoke tobacco products? | Daily  5-6 days a week  3-4 days a week  1-2 days a week  Occasionally | 1  2  3  4  5 | T4 |
| **Alcohol consumption** | | | |

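### New and known type 2 diabetes are enrolled together, but new/known status is neither a randomisation stratum nor a listed baseline item: a possible loss of precision that is cheap to avoid

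*Protocol*

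**What the plan says.** Section 7.3 (Study population/Sampling frame) draws both arms from "known cases of T2DM and newly diagnosed cases of T2DM patients who are within 25-64 years of age group". It sets no split or cap between the two kinds of patient. The inclusion criteria in section 7.7 ask for "HbA1c>48 mmol/mol (6.5%) at time of diagnosis" and put no limit on time since diagnosis.

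Section 7.2 describes a "two-arm RCT with equal allocation of participants between the intervention and control group/usual care arm". Section 7.12, on the randomisation process, says that "participants will be enrolled in either intervention or control groups randomly using computer generated random numbers". It mentions no strata, blocks or minimisation.

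The independent variables in section 7.8 are, on the socio-demographic side, "Age, Sex, Education level, Occupation, Religion, Marital status, Residence, Smoking habit, and Alcohol habit". On the clinical side they include HbA1c, other laboratory values and "Body mass index (BMI), Waist hip ratio (WHR), Physical activity level, Current medication used". In the main study questionnaire the nearest item on disease history is "Family history of Diabetes Mellitus" (C10), followed later by blank lines for current medication (M1–M14). Date of diagnosis, diabetes duration and new/known status appear in neither place. Section 7.10 also mentions a screening checklist: "This checklist entails information regarding inclusion and exclusion criteria". The form itself is not reproduced.

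For analysis, the project summary names an independent-sample t-test of changes between arms. The statistical analysis section adds a linear regression for the primary and secondary outcomes without naming covariates.

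**The concern.** The primary outcome is the change in HbA1c from baseline to six months. A newly diagnosed patient may be starting management at about the time of baseline in either arm, whereas a known case may have been on a settled regimen for years. The eligibility value shows the contrast: HbA1c at diagnosis is close to the baseline value for a new case, but may be old for a known one. If new cases improve more whatever their arm, new/known status predicts the outcome, and leaving it out of both design and model wastes precision.

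Strata and baseline data items are fixed by the protocol and its forms. A later analysis plan can choose covariates, but it cannot adjust for, or tabulate by arm, a variable that was not collected.

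**Working it through.** **Inputs from the protocol (sample size section):** two-sided 5% level (z = 1.96), power 90% (z = 1.282), S = 0.1, d = 0.64 in absolute value, 54 per arm before inflation and 78 per arm after it.

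**The plan's own figure.** n per arm = 2(1.96 + 1.282)² S²/d².
- With the printed S = 0.1: 21.02 × 0.01/0.4096 = 0.5, so 1 per arm. This does not reproduce 54.
- With S = 1.0: 21.02/0.4096 = 51.3, so 52 per arm. This is close to 54.
- Solving for S at 54 per arm and d = 0.64: 0.64 × √27/3.242 ≈ 1.03.

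An SD of about 1.0 is therefore inferred from the stated sample size; the protocol does not give it. The discrepancy with S = 0.1 is a separate matter.

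**Assumptions not in the documents:** share newly diagnosed p, 0.15–0.50 (wider range 0.10–0.50); extra six-month fall in new cases D, 1.0 HbA1c point in both arms (wider range 0.5–1.5); SD within each of the two patient groups, 1.0.

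**Formulas.** SD of change = √(1 + p(1−p)D²). Half-width of the 95% interval = 1.96 × SD × √(2/54). Power = Φ(0.64/(SD × √(2/54)) − 1.96). Here √(2/54) = 0.1925.

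| p | D | SD of change | 95% half-width | Power, 54 per arm |
|---|---|---|---|---|
| no mixture | – | 1.000 | 0.377 | 91.4% |
| 0.10 | 0.5 | 1.011 | 0.381 | 90.8% |
| 0.15 | 1.0 | 1.062 | 0.401 | 87.9% |
| 0.30 | 1.0 | 1.100 | 0.415 | 85.6% |
| 0.50 | 1.0 | 1.118 | 0.422 | 84.5% |
| 0.50 | 1.5 | 1.250 | 0.472 | 75.8% |

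If all 78 per arm were analysed, power would be 97.9% with no mixture, 95.3% at p = 0.30 and D = 1.0, and 89.2% at p = 0.50 and D = 1.5.

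**Chance imbalance is the same quantity, not a second harm.** Under simple randomisation the between-arm difference in the share of new cases has variance 2p(1−p)/54, so it adds 2p(1−p)D²/54 to the variance of the HbA1c contrast. At p = 0.30 and D = 1.0 this is 0.42/54 = 0.0078. The mixture raises the variance of the contrast from 2/54 = 0.0370 to 2 × 1.21/54 = 0.0448, an increase of the same 0.0078. The t-test's standard error already carries it.

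**If 1.0 is the total SD instead.** Planned power stays at about 91% and nothing is lost against plan. Adjusting for the stratum would then be a gain: at p = 0.30 and D = 1.0 the residual SD is √(1 − 0.21) = 0.889 and power is about 96%.

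**The case against.** The other side has a good deal to say.

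- **The premise is outside the documents.** Nothing in the protocol says that HbA1c falls more after a new diagnosis, or by how much, and the share of new cases is not given. This stands: every figure for the loss is conditional. Eligibility may also narrow the contrast, since patients on insulin or with HbA1c of 10.5% or above are excluded.
- **Simple randomisation is valid.** A reader might infer that a chance excess of new cases in one arm would bias the result or pass for a diet effect. The documents do not support that. Randomisation keeps the estimate unbiased in expectation, and the standard error covers the imbalance.
- **The recorded data help.** A reader might infer that the extra variation cannot be removed at all. Baseline HbA1c and current medication are collected and a regression is planned, so part of it can be adjusted for. The proxies are incomplete: baseline HbA1c is a level and not a trajectory, and the medication lines show no start date. The unseen checklist might also hold the diagnosis date, so the omission is shown only for the variable list and the questionnaire.
- **The planning SD may already include the mix.** A reader might infer that the trial is less powerful than planned. The SD of 1.0 is solved back from 54 per arm and may be the total SD, in which case no power is lost against plan.
- **Covariates can be left to an analysis plan.** True, and their absence is not the complaint. The complaint is the missing item and stratum.

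**Conclusion.** The point holds as a modest, precision-only improvement. Two kinds of patient with possibly different HbA1c courses are randomised with no stated stratum, and the variable list and questionnaire contain nothing that identifies them directly. As written, the trial could not tabulate new/known status by arm or adjust for it other than through proxies.

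The size rests on assumed values. With an extra fall of 1.0 point, the interval for the HbA1c difference widens by about 6–12% and power at 54 per arm falls by some 3 to 7 percentage points. Over the wider range, the result runs from almost no loss to power of about 76%. The documents cannot say where in that range the trial lies. They support neither a claim of bias nor a firm claim that the sample is too small for this reason.

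**What to change.** 1. Add one baseline item to the questionnaire and to section 7.8: date of diabetes diagnosis, or newly diagnosed yes/no with a stated definition.
2. In section 7.12, generate the computer list in two strata, new and known, with permuted blocks. Because the trial is open-label, keep the block sizes from the staff who enrol.
3. In the statistical analysis section, include the stratum and baseline HbA1c as covariates in the HbA1c regression. Under the working assumptions, including the stratum brings the residual SD back to 1.0 and the half-width to about 0.38.

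The cost is one questionnaire item, two lists instead of one, and the covariates in a regression already planned. No extra patients, visits or tests are needed.

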## **7.4. Study site and its justification**

The study will be conducted in Tribhuvan University Teaching Hospital (TUTH) in Kathmandu, Nepal where superspecialist services is available with high patients flow.

## **. Sampling method**

1. **Non probability:** This study will utilize non-probability purposive sampling methods to choose the tertiary care hospital in Kathmandu metropolitan city.
2. **Probability sampling:** Simple random sampling will be used to select the desired number of participants.

## **. Sample size**

Since, there was no similar research carried out in Nepal thus the sample size has been calculated based on the similar study conducted by JW Muchiri et al., (2010) in South Africa where, mean+ SE of HbA1c percentage in both intervention and control group was 9.67±0.29 Vs 10.30±0.29 respectively ^20^. Based on this consideration, JW Muchiri et al., (2010) data will be used to calculate the sample size taking α level of significance at 5% and power of 90%. The sample size will be calculated using test comparing independent two means in STATA/MP version 14.1 (StataCorp LP, College Station, Texas). The following formula with 5% significance level (Zα/2 = 1.96) and 90% power (Zβ) will be used.

Where

Z_α_ = Z value for α error

Z_β_ = Z value for β error

S = Common standard deviation between two groups

d = clinically meaningful difference

Z_α_=1.96, Z_β_= 1.282, S= 0.1, d= -0.64

The sample size will be calculated 108 (54 participants in each arm). Thus, the sample size will be adjusted with 20% non-response rate and 25% loss through follow-up and drop out the total sample size will be 156 (78 participants in Intervention and 78 participants in usual care arm respectively.)

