# **Plan for data management and statistical analysis**

- **Data entry:** A data entry program will be developed using EpiData version 3.0. A number of skips and ranges will be developed to ensure data entry. Trained data entry professionals will enter the data. After the data entry, a thorough check and cleaning of data will be done to maintain consistency.
- **Data analysis:** Data will be analyzed on an intention-to-treat analysis. Data will be analyzed using STATA/MP version 14.1 (StataCorp LP, College Station, Texas). A number of statistical analysis will be done to analyze the data which are listed below:
- **Normality test:**The normality of data will be assessed using the Kolmogorov-Smirnoff test and visual inspection of Q-Q plots. Normally distributed data will be presented as means with standard deviation whereas non-normally distributed data will be expressed as medians with interquartile ranges.
- **Descriptive statistics**: Descriptive statistics will be carried out for socio-demographic information. Frequency, percentage, mean (standard deviation) and median (inter-quartile range) will be calculated under descriptive statistics.
- **Chi-square test**: Chi-square or Fisher exact test will be used to analyze between the intervention and usual care arm for categorical variables.
- **Independent sample t-test:** Difference between intervention and usual arm will be applied using independent sample t-test assuming equal variance if data is normally distributed for continuous variables (two-tailed; parametric).
- **Mann-Whitney U test**: Mann-Whitney U test will be used to compare the medians of continuous variables if in case the assumption for independent sample t-test will be violated (two-tailed; non-parametric).
- **Linear regression**: A linear regression analysis will be used to model the primary and secondary outcome measures.

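### The stated 90% power is not established for the stated primary test: the sample size rests on HbA1c levels, the primary outcome is change in HbA1c, and no SD of change or correlation is given

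*Protocol*

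**What the plan says.** **Sizing.** In the protocol's Sample size section the inputs come from a cited trial: "mean+ SE of HbA1c percentage in both intervention and control group was 9.67±0.29 Vs 10.30±0.29 respectively". The calculation is specified as "taking α level of significance at 5% and power of 90" percent, and "The sample size will be calculated using test comparing independent two means in STATA/MP version 14.1". S is described as the SD common to the two groups. The printed values are S = 0.1 and d = -0.64, with a result of 54 per arm (108), raised to 78 per arm (156) for non-response and dropout. The section does not say at which visit the two means were taken. It mentions no change score, SD of change or correlation.

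**Outcome and test.** The Project summary says "The primary outcome of the study will be a difference in mean change (from baseline, midline to 6 months) in the HbA1c level" between the arms, and that an independent-samples t-test "will be used to estimates changes between the intervention and usual care arms". The first specific objective also speaks of change in HbA1c.

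**Elsewhere.** Section 7.8 (Study variables) lists the dependent variable simply as the HbA1c level. The statistical analysis section applies the t-test to the difference between arms, "assuming equal variance if data is normally distributed for continuous variables (two-tailed; parametric"), without saying whether level or change is tested. It adds a linear regression for the primary outcome without naming covariates.

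**The concern.** A power figure belongs to one test statistic and its SD. Under randomisation the expected between-arm difference is the same for the follow-up level and for the change from baseline, so the target difference carries over. The SD does not, because the SD of a change depends on the SDs at both visits and on the correlation between them. A plan sized with an SD of level and tested on change has the stated power only if the two SDs happen to be equal. With no correlation or SD of change in the protocol, nobody can check whether they are. At stake is whether the trial has its advertised 90% chance of detecting the target difference on its primary outcome.

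**Working it through.** **Inputs from the protocol.** Two-sided 5% (Z = 1.96) and 90% power (Z = 1.282); means 9.67 and 10.30, so the difference is 10.30 - 9.67 = 0.63 (0.64 is printed); SE 0.29 per group; S = 0.1; 54 per arm.

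**Assumed, because the protocol gives none.** r, the baseline to 6-month correlation of HbA1c, and the SD at each visit.

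**Step 1: the plan's own figure.** Normal formula: n per arm = 2 × [S × (1.96 + 1.282) / d]².

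- Printed values, S = 0.1 and d = 0.64: 2 × (0.1 × 3.242 / 0.64)² = 0.51, so 1 per arm, not 54.
- S = 1.0 and d = 0.63: 2 × (3.242 / 0.63)² = 52.96, so 53. The t-test version gives exactly 54, with power 90.0%.
- S = 1.0 and d = 0.64: 52 by the normal formula, 53 by the t version.

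So 54 needs an SD near 1.0. That value is back-solved and is not printed anywhere. It does not follow from the SE either: SD = 0.29 × √m for m patients per source group, and 0.29 × √12 = 1.005, so any source group of 12 or more implies an SD above 1.0. For an assumed m of 30 to 54 the SD is 1.59 to 2.13, and power with 54 per arm at d = 0.63 falls to 53% to 33% for a comparison of levels.

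**Step 2: the SD of change.** In general SD(change) = √(SD0² + SD1² - 2 r SD0 SD1), where SD0 is the baseline SD and SD1 the follow-up SD. If both equal S this becomes S × √(2(1 - r)), which equals S only at r = 0.5.

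**Step 3: power of the t-test on change.** 54 per arm, d = 0.63, two-sided 5%, noncentral t, SD assumed to be 1.0 at both visits:

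| r | SD of change | Power |
| --- | --- | --- |
| 0.2 | 1.265 | 73% |
| 0.3 | 1.183 | 78% |
| 0.4 | 1.095 | 84% |
| 0.5 | 1.000 | 90% |
| 0.6 | 0.894 | 95% |
| 0.7 | 0.775 | 99% |

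**Step 4: unequal SDs.** Keep the follow-up SD at 1.0 and let the baseline SD be smaller.

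- Baseline SD 0.7, r = 0.3: √(1 + 0.49 - 0.42) = 1.034, power 88%. At r = 0.4: √(1 + 0.49 - 0.56) = 0.964, power 92%.
- Baseline SD 0.8, r = 0.3: √(1 + 0.64 - 0.48) = 1.077, power 85%. At r = 0.4: √(1 + 0.64 - 0.64) = 1.000, power 90%.

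The level and change SDs then match at r = SD0 / (2 × SD1), that is 0.35 and 0.40, rather than 0.5.

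**Step 5: a baseline-adjusted analysis.** The residual SD is S × √(1 - r²). With S = 1.0 and r = 0.3 it is 0.954, and power is about 93%. This SD never exceeds S, so adjustment would not lose power against the level comparison.

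**The case against.** The strongest reply has four parts.

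- **The sizing sentence fits a test on change.** A t-test on change scores also compares two independent means. This stands. The mismatch shows only when the source means and the description of S are set against the outcome definition in the Project summary. That S is an SD of level is the natural reading of that section, but the protocol does not spell it out.
- **The protocol is not uniform about what is tested.** Section 7.8 names the level, the analysis section does not name change, and a regression is also planned. This stands too. It is therefore too strong to say that the 90% belongs to a test the trial never runs. But the only explicit primary outcome statement is on change, so the power still has to be shown for that statistic, or the outcome statement has to be altered.
- **The choice of S matters more than level against change.** This is correct. The powers in Step 3 hold only for an SD of 1.0. The printed inputs do not support 90% for a comparison of levels either.
- **The direction is open.** Correct: power is below 90% at low r and above it at high r.

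A reader might infer that the trial is underpowered because the entry window for HbA1c is narrow (cases at 10.5% or above are excluded) and a narrow window lowers r. The documents do not support this. They give no r, and a window that narrows the baseline spread also makes the baseline SD smaller than the follow-up SD. That offsets much or all of the loss, as Step 4 shows. A reader might also take 9.67 and 10.30 as end-of-study values, but the section names no visit.

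**Conclusion.** The point holds in a limited form. The sizing inputs are HbA1c levels, the defined primary outcome is a difference in mean change, and nothing in the protocol links the two. The 90% power is therefore not established for the stated primary test.

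The size of the error cannot be fixed from the protocol. Under the assumption of an SD of 1.0 at both visits, it runs from 12 points too high (r = 0.3) through nil (r = 0.5) to 9 points too low (r = 0.7). A smaller baseline SD raises the power at low r; an SD above 1.0 at both visits lowers it at every r. This is not a finding that the trial is underpowered, nor that 156 is the wrong number. Equally, nothing here supports simply keeping 156 on a 90% basis while S is unsettled.

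**What to change.** 1. Name one primary test statistic, either the 6-month level, the change from baseline, or a baseline-adjusted comparison. Use it consistently in the Project summary, in section 7.8 and in the statistical analysis section.
2. In the Sample size section, give the SD that belongs to that statistic, with its source: the SD of change, or the level SDs at both visits plus an assumed r. For a baseline-adjusted analysis use S × √(1 - r²).
3. In the same recalculation, correct S, since 0.1 neither gives 54 per arm nor follows from an SE of 0.29. Reconcile d, which is 0.63 from the means and 0.64 as printed. State the visit to which the cited means refer.
4. Replace the single 90% with the power that the planned 156 gives, after the stated losses, over a range such as r = 0.3 to 0.7.

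The cost is one rewritten paragraph, small wording changes in three places and one recalculation. The restated power may be less favourable than 90%. Whether 156 remains adequate can be judged only once S is corrected.
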